## Abstract

Background and purpose — Dislocation is the leading reason for early revision surgery after total hip arthroplasty (THA). The dual-mobility (DM) cup was developed to provide more stability and mechanically reduce the risk of dislocation. Despite the increased use of DM cups, high-quality evidence of their (cost-)effectiveness is lacking. The primary objective of this randomized controlled trial (RCT) is to investigate whether there is a difference in the number of hip dislocations following primary THA, using the posterolateral approach, with a DM cup compared with a unipolar (UP) cup in elderly patients 1 year after surgery. Secondary outcomes include the number of revision surgeries, patient-reported outcome measures (PROMs), and cost-effectiveness.

Methods and analysis — This is a prospective multicenter nationwide, single-blinded RCT nested in the Dutch Arthroplasty Registry. Patients ≥ 70 years old, undergoing elective primary THA using the posterolateral approach, will be eligible. After written informed consent, 1,100 participants will be randomly allocated to the intervention or control group. The intervention group receives a THA with a DM cup and the control group a THA with a UP cup. PROMs are collected preoperatively, and 3 months, 1 and 2 years postoperatively. Primary outcome is the difference in number of dislocations between the UP and DM cup within 1 year, reported in the registry (revisions), or by the patients (closed or open reduction). Data will be analyzed using multilevel models as appropriate for each outcome (linear/logistic/survival). An economic evaluation will be performed from the healthcare and societal perspective, for dislocation and quality adjusted life years (QALYs).

Trial registration — This RCT is registered at www.clinicaltrials.gov with identification number NCT04031820.

Dislocation after total hip arthroplasty (THA) is the leading reason for early revision surgery (Bozic et al. 2009, Gwam et al. 2017). Most dislocations occur during the first year after surgery, of which approximately half within the first 3 months (Woo and Morrey 1982, Phillips et al. 2003, Meek et al. 2006, Hailer et al. 2012). Especially in patients with recurrent dislocation and the need for revision surgery, this leads to reduced physical functioning and quality of life (Enocson et al. 2009). Dislocations also increase healthcare costs (Sanchez-Sotelo et al. 2006, Abdel et al. 2015). A single dislocation adds 19% to the hospital costs of an uncomplicated THA, and of a revision surgery up to 148% (Sanchez-Sotelo et al. 2006).

Despite the increased and, in some countries, broad use of DM cups, high-quality evidence of their effectiveness is lacking (Darrith et al. 2018). Recent reviews did not identify any randomized controlled trials (RCT) comparing DM cups with UP cups (De Martino et al. 2017a, 2017b, Darrith et al. 2018, Jonker et al. 2020) and the existing studies are of low methodological quality and at high risk of bias due to the lack of experimental design. So far only one—non randomized—cost-effectiveness study has been performed, suggesting that the DM cup may result in cost savings compared with a UP cup (Epinette et al. 2016). Although promising, the results of this cost-effectiveness database study are not transferrable outside France.

Therefore we initiated an RCT to establish the effectiveness of DM cups for primary THA. The primary objective is to investigate whether there is a difference in the number of hip dislocations following primary total hip arthroplasty (THA), using the posterolateral approach, for a DM cup compared with a UP cup in elderly patients within 1 year after surgery. Several secondary outcomes will be specified in the methods section. The registry-nested design will facilitate long-term follow-up for all study participants.

## ^Methods and analysis^

### ^Study design^

This is a prospective registry-nested multicenter single-blinded RCT, which will be conducted in 10 general and academic hospitals in the Netherlands. This RCT compares the number of hip dislocations following primary THA with a DM cup compared with a UP cup and is nested in the Dutch Arthroplasty Registry (LROI).

All patients will be followed up until 2 years after surgery. The recruitment phase started in April 2019 and was anticipated to last 2.5 years. After the first year of recruitment, we have experienced a slight delay. After final study follow-up, participants remain traceable in the LROI for evaluation of long-term survival and mortality.

### ^Participants^

All patients at the orthopedic outpatient clinics of participating centers that meet the criteria to undergo an elective primary THA will be screened for the in- and exclusion criteria.

Patients can be included when they are 70 years or older; have adequate comprehension of written and spoken Dutch; and are eligible for elective primary THA with a cup large enough for a 32 or 36 millimeter head diameter, by a surgeon who is comfortable using the posterolateral approach. A previous contralateral THA is not a reason for exclusion, but patients who undergo bilateral hip arthroplasty can only participate in the trial with 1 of the hips. Patients will be excluded when they: are not able to complete PROMs; are not eligible for either a UP or DM cup; have epilepsy, spasticity, dementia, mental retardation, or alcoholism. If dementia or mental retardation is not already mentioned in the medical chart, this can be determined by doctor’s opinion.

Characteristics that will be collected are: age; sex; BMI; smoking; diagnosis; ASA classification; Charnley score; education level according to the Statistics Netherlands classification; surgical details (e.g., side, any complications); implant details (e.g., brand, size); type of fixation (cemented or uncemented); type of stem.

### ^Interventions^

All patients participating in the RCT will be treated with a THA using the posterolateral approach. Patients are randomly allocated to a DM cup or to a UP cup with a 1:1 allocation ratio. It is a requirement for participating surgeons to feel confident with both procedures. The Dutch guidelines recommend reconstruction of the capsule and external rotators when using the posterolateral approach. There are no restrictions to a specific brand of implant, and participating hospitals can use the implants of the companies they usually work with. This study does not investigate any specific implant, but rather pragmatically the concept of DM cups. The Avantage (Zimmer Biomet, Warsaw, IN, USA) and POLAR (Smith & Nephew, London, UK) cups are examples of commonly used DM cups. The IP (Link, Hamburg, Germany), FAL (Link), Exeter (Stryker, Kalamazoo, MI, USA) and Pinnacle (Johnson & Johnson, New Brunswick, NJ, USA) cups are commonly used UP cups. Cemented DM and UP cups have 5-year survival rates of ≥ 96%, with cumulative revision rates ranging from 1.9% to 4.0% when revision was defined as any change (insertion, replacement, and/or removal) of one or more components of the prosthesis, for any reason (LROI 2017b). Lubinus SP2 (Link), Exeter (Stryker), and Corail (Johnson & Johnson) are the commonly used stems.

All patients receive the same standard pre- and postoperative care for both DM and UP cups according to their hospital’s standard.

### ^Sample size calculation^

Exact dislocation rates in the Netherlands are unknown, as only those dislocations that result in revision surgery are registered. Based on previous studies and reviews, we assume that the current dislocation rate for UP cups is 4% whereas DM cups result in 1% dislocation (Philippot et al. 2009b, Boyer et al. 2012, Fresard et al. 2013, Prudhon et al. 2013, Caton et al. 2014, Batailler et al. 2017, De Martino 2017a). Power analysis indicates that a total sample of 976 (488 in each group) is needed to detect a difference in dislocations between 4% in the UP cup group and 1% in the DM cup group, using the chi-square test with 80% power and α = 0.05. To account for loss to follow-up, 550 patients will be included in each group.

### ^Outcomes^

#### Primary outcome

The primary outcome is the number of hip dislocations, regardless of type of treatment. This information is collected from both the LROI and the patient. Since the LROI registers only revisions, open and closed reductions would be missed. Therefore, patients are asked with a questionnaire at 3 months, 1- and 2-year follow-up whether they have had a hip dislocation.

#### Secondary outcomes

Secondary outcomes are any unplanned hip procedures, including revision surgery of any component, for any reason; cost-effectiveness; and PROMs.

The following PROMs are collected preoperatively, and 3 months, 1 and 2 years postoperatively: Physical functioning of the hip measured with the Hip disability and Osteoarthritis Outcome Score Physical Short form (HOOS-PS) (de Groot et al. 2007); Quality of life measured with the EuroQol 5 Dimensions (EQ-5D) (EuroQol 1990); pain measured with a numeric rating scale (NRS) ranging from 0 to 10 for pain at rest and during weight-bearing; change in physical functioning measured with an anchor question; fear of hip dislocation measured on a five-point Likert scale. At all postoperative moments, the awareness of type of cup that was placed is asked.

At 3 months and 1 year postoperatively healthcare and societal costs related to hip dislocation or surgery are measured with a retrospective 4-week cost evaluation questionnaire, which is filled out by the patient. We will obtain information on health care utilization, (pain) medication used, patient costs, use of domiciliary care, use of informal care, and sickness absenteeism from paid or unpaid work. Healthcare utilization consists of general practitioner care, allied healthcare, medical specialist care, imaging tests, admission to a hospital, rehabilitation center, nursing home or care home, and mobility aids. Participants’ costs concern the patient contribution towards costs for mobility aids and travel. Domiciliary care consists of home nursing care and home help. Healthcare utilization, domiciliary care, informal care, and sickness absenteeism will be valued at Dutch standard costs (Hakkaart-van Roijen et al. 2015). If these are not available, prices reported by professional associations will be used. The costs of prescribed medications will be calculated using prices charged by the Royal Dutch Society for Pharmacy.

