#### Secondary outcomes analyses

Secondary study outcomes are any surgical intervention on the affected hip including revision surgery, healthcare costs, societal costs, patient-reported physical functioning, quality of life, pain, satisfaction, fear of hip dislocation and device-related complications and reoperations. The secondary outcomes will be analyzed using similar multilevel models as appropriate for each outcome (linear/logistic/survival).

An economic evaluation will be performed from the healthcare and societal perspective, for dislocation and quality adjusted life years (QALYs). Prevailing guidelines of Zorginstituut Nederland will be observed. All costs and consequences relevant to THA, hip dislocation, and hip revision will be accounted for.

To compare costs between groups, confidence intervals around the mean differences in costs at one year after THA will be estimated using the bias-corrected and accelerated bootstrap method. To account for possible clustering of data and to adjust for possible confounders, multi-level analyses will be performed. To present the incremental cost-effectiveness ratios and uncertainty around them graphically, bootstrapped cost-effect pairs will be plotted on cost-effectiveness planes. Cost-effectiveness acceptability curves will present the probability that the DM cup is more cost-effective than the UP cup for a range of willingness-to-pay thresholds. To study the robustness of these results, sensitivity analyses will be performed.

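### The cost questionnaire covers 8 of the 52 weeks and about 80% of dislocations start outside it, so it cannot by itself support the one-year cost comparison

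*Protocol article*

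**What the plan says.** All references are to the protocol article.

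- **Secondary outcomes, instrument and timing:** "healthcare and societal costs related to hip dislocation or surgery are measured with a retrospective 4-week cost evaluation questionnaire". Patients complete it twice, at 3 months and at 1 year; no other time point is given for costs.
- **Secondary outcomes, content:** the questionnaire is not confined to routine care. Its items include "medical specialist care, imaging tests, admission to a hospital, rehabilitation center, nursing home or care home, and mobility aids", together with home care, informal care and absence from work.
- **Secondary outcomes analyses, target:** "confidence intervals around the mean differences in costs at one year after THA will be estimated", from a healthcare and a societal perspective.
- **Secondary outcomes analyses, completeness:** "All costs and consequences relevant to THA, hip dislocation, and hip revision will be accounted for". Sensitivity analyses are planned, but their content is not given.
- **Primary outcome, separate event capture:** revisions come from the registry, and "patients are asked with a questionnaire at 3 months, 1- and 2-year follow-up whether they have had a hip dislocation". No 4-week limit is attached to that question.
- **Introductory text, timing of events:** "Most dislocations occur during the first year after surgery, of which approximately half within the first 3 months".

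The article does not say how costs in the weeks outside the two windows are obtained.

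**The concern.** A short recall window works for steady, frequent use such as general practitioner visits or home help, because a 4-week sample resembles the weeks around it. A dislocation is different: it is a rare, costly, one-off episode (reduction, admission, sometimes revision), and a 4-week window either contains it or misses it entirely. The article nevertheless places hospital admission and specialist care in the 4-week instrument and draws a one-year comparison from it.

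The Discussion says the economic evaluation should show whether the dual-mobility (DM) cup, described as typically dearer, is worthwhile. Avoided dislocations are an offsetting saving that the comparison must capture. At the assumed rates (4% with the unipolar (UP) cup, 1% with DM) four in five dislocations occur in the UP group, so episodes that go uncosted are mostly UP episodes.

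**Working it through.** **Plan's own figure.** The article states no coverage figure for the cost windows. Its sample size can be checked because the same rates are used below: 4% v 1%, two-sided 5%, 80% power, with continuity correction, gives 489 per group against 488 stated. The figures agree within rounding.

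**Inputs from the article.** Recall 4 weeks; time points 3 months and 1 year; horizon 52 weeks; about half of first-year dislocations in the first 3 months; 4% and 1%; 488 per group required and 550 recruited; one dislocation adds 19% to the hospital costs of an uncomplicated total hip arthroplasty (THA).

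**Assumptions not in the article.** Each window is the 4 weeks just before its time point (weeks 9–13 and 48–52 of elapsed time). The shape of event timing within each period is assumed and varied.

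**Step 1, calendar coverage.** 2 × 4/52 = 15.4%, so 44 weeks (84.6%) are uncovered.

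**Step 2, share of dislocations starting inside a window.** With share *s* in weeks 0–13, and timing uniform within weeks 0–13 and 13–52, the share is *s* × 4/13 + (1 − *s*) × 4/39.

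| Timing assumption | Inside | Outside |
|---|---|---|
| Uniform within periods, *s* = 0.5 | 20.5% | 79.5% |
| Uniform within periods, *s* = 0.4 | 18.5% | 81.5% |
| Uniform within periods, *s* = 0.6 | 22.6% | 77.4% |
| Exponential decline, half by week 13 | 12.3% + 2.0% = 14.3% | 85.7% |
| F(t) = √(t/52), half by week 13 | 8.4% + 3.9% = 12.3% | 87.7% |

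If care is assumed to last 2 to 12 weeks after each event, about 78% to 87% of that care still falls outside the windows.

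**Step 3, number of captured events.** With 488 per group, expected dislocations are 488 × (0.04 + 0.01) = 24.4, and 24.4 × 0.205 = 5.0 fall in a window. With 550 per group the figures are 22 (UP) and 5.5 (DM), of which about 4.5 and 1.1 are captured.

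**Step 4, consequence under each possible costing rule.**

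- *Windows summed, unscaled.* About 12% to 21% of event costs are seen, on the *s* = 0.5 rows above. At 19% per dislocation, a 3-point reduction is worth 0.03 × 19% = 0.57% of an index THA's hospital costs per patient. With uniform timing, 0.57% × 0.205 = 0.12% would be observed.
- *Each window scaled to its period.* The multipliers are 13/4 = 3.25 and 39/4 = 9.75. Expected recovery is 0.5 × (4/13) × 3.25 + 0.5 × (4/39) × 9.75 = 100% with uniform timing. It is about 59% with exponential decline and 66% with the square-root curve. For rare events of a given cost, variance relative to full capture is 0.5 × (4/13) × 3.25² + 0.5 × (4/39) × 9.75² = 0.5 × 3.25 + 0.5 × 9.75 = 6.5, so the standard error rises by √6.5, about 2.5. This applies to the episode-cost component only.
- *Recorded events costed at unit prices.* The reduction and revision costs need not be lost.

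**The case against.** The strongest reply is that the questionnaire is named as an instrument, not as the only one. Dislocations are captured over the whole year from patients and the registry. The Discussion describes the patient-reported part as dislocations treated by closed or open reduction, so treatment type may be known. Unplanned hip procedures and revisions are secondary outcomes, and serious adverse events are tracked. Neither window can contain the index operation, so a costing that includes THA must draw on another source. The completeness sentence may therefore signal event-based costing, and a condensed article may leave that rule to a fuller document.

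Much of this stands. A reader might infer that the one-year cost difference will be wrong, or is bound to be biased against the DM cup. The article does not support that. No passage proposes summing the windows unscaled, and scaling recovers the full expected cost if timing is uniform within periods. The under-recovery of 59–66% depends on assumed front-loading. A reader might also use the 148% revision figure to put the saving at 0.03 × 148% = 4.4% of an index THA per patient. That would need every averted dislocation to be revised at the upper limit of cost.

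Two things remain. First, the article places hospital admission and specialist care in the 4-week instrument and never links the full-year event data to costing. Second, for rehabilitation, nursing-home stay, home care, informal care and absenteeism after a dislocation, the two windows are the only source described. Neither a later analysis plan nor a sensitivity analysis can recover resource use that was never asked about.

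**Conclusion.** The point holds as a limit on the instrument. As described, the questionnaire observes 15.4% of the year, and about 80% of first-year dislocations (77–88% across the timing assumptions) start outside it. Alone, it cannot support the one-year cost comparison or the statement that all dislocation and revision costs are counted. Unscaled sums would understate the saving from fewer dislocations; scaling would rest on about 5 events, with a roughly 6.5-fold variance for episode costs.

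It is not shown that the final cost difference will be wrong, because the size and direction of any bias depend on the unstated costing rule. Nor is it shown that total cost becomes 6.5 times more variable, since total cost has other components. The result rests on the assumed position of the windows and on the assumed timing within periods. Cost-effectiveness is a secondary outcome; the primary outcome is untouched.

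**What to change.** 1. State that every recorded dislocation, reduction and revision in the first year is costed as an event: count from the patient questionnaires and the registry, multiplied by unit prices. Confirm that the dislocation item yields number and treatment, since the article describes only whether one occurred.
2. For patients still in follow-up, change the recall for hospital care and institutional admissions (hospital, rehabilitation center, nursing or care home) to the period since the operation at 3 months, and since the last questionnaire at 1 year.
3. Keep the 4-week recall for routine items only (general practitioner, allied care, home care, informal care), and state that they are interpolated between time points.
4. State that episodes costed under step 1 are not counted again from the questionnaire.

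**Cost.** A few reworded items and a paragraph of analysis text. Event costing largely uses data already collected, including for patients past a time point. Longer windows bring somewhat more recall error, likely minor for hospital episodes. Home and informal care after a dislocation would still be seen only in the windows, which should be reported as a limitation.

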### ^Study procedures^

#### Informed consent

During the preoperative visit at the outpatient clinic, patients who are potential candidates for this study will be screened to determine whether they meet the in- and exclusion criteria. If the patient is eligible, the investigator (or his designated representative) will propose participation in the study to the patient, according to GCP guidelines. Patients must sign an informed consent form approved by the ethical committee, prior to participating in any study-specific related activities.

#### Randomization

After signing informed consent, 1,100 patients will be randomized to either the intervention group (DM cup) or the control group (UP cup). Each group will consist of 550 patients. The investigator (or his designated representative) will perform the randomization using the platform CASTOR Electronic Data Capture (www.castoredc.com). Variable randomization blocks of 2, 4, and 6 patients will be used, and we shall stratify for center. Patients will be blinded for treatment allocation. The participating surgeons may divert from the randomization scheme based on intraoperative findings. Any deviation from the assigned treatment group will be reported as a deviation from the protocol.

#### Follow-up

Patients are evaluated at 3 months, 1 year and 2 years after surgery.

### ^Data analysis plan^

#### Interim analysis

Interim analysis for the primary study outcome will be performed when 200 patients have reached the 3 months postoperative PROM evaluation point. In the interim analysis the number of dislocations in each group will be compared. A chi-square test will be used and in any case where the assumptions of this test are not met, Fisher’s exact test will be applied. To guard against a type 1 error, we will use the O’Brien–Fleming approach. As only 1 interim analysis will be performed, the alpha for this analysis is set at 0.005. Testing will be done 2-sided. Furthermore, we will consider the number of revisions and SAEs in each group, but not formally test for differences in these. Results of the interim analysis will be discussed with the study team, the Van Rens Foundation (funder of this study), and the ethical committee. In the case of a statically significant and relevant higher number of dislocations in the DM group, or more revisions or SAEs, appropriate actions will be taken (such as an early termination of the study).

#### Primary outcome analysis

The primary outcome, the difference in number of dislocations in both groups, will be analyzed using chi-square analysis. Additional exploratory multivariable logistic regression analyses will adjust for clustering of data (e.g., at the hospital level), and possible confounding or effect modification of patient and surgical characteristics (e.g., age; sex; BMI; smoking; diagnosis; ASA classification; Charnley score; education level according to the Statistics Netherlands classification; surgical details; implant details; type of fixation; type of stem). A multilevel survival model will be used to analyze the survival of the implant, corrected for covariates.

Analyses will be performed using both intention-to-treat as well as per-protocol analysis.

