Our registry-nested randomized design is an efficient way to obtain an unbiased comparison between DM and UP cups, both in the short term and long term. Currently, dislocations are only reported in the registry if they result in implant revision. Therefore, the primary—relevant to patients—outcome of this study is a composite measure of revisions due to dislocation reported in the registry and patient-reported dislocations that were treated with closed or open reduction. Not many studies used such a composite outcome, which complicated our sample size calculation. The current group sizes are based on informed assumptions, and considered large enough to detect substantial differences between groups. However, regarding this limitation we believe it is fair to compare groups in terms of dislocation rates with corresponding confidence intervals rather than strictly focusing on p-values (Wasserstein and Lazar 2016). Also, the registry-nested design does allow for comparison with large groups of patients who underwent similar hip replacement surgery outside the study. Another limitation is that we do not collect radiographic outcomes for each participant.

The literature shows good survival rates up to 10 years for DM cups, ranging from 90.4% to 100% (Clave et al. 2016, Martz et al. 2017, Puch et al. 2017, Tarasevicius et al. 2017, Laurendon et al. 2018, Spaans et al. 2018, Cypres et al. 2019, Fessy et al. 2019, de l’Escalopier et al. 2020). Nevertheless, our population includes only patients aged 70 and older to minimize risk of revision for other indications such as loosening and wear. The study results may therefore promote additional research with a younger study population that is generally more active.

Important strengths of this study are that we will keep track of complications (serious adverse events) other than dislocations as well. In the long term, we shall be able to study survival of the implants as well as mortality in both study groups, as these remain available in the LROI. Finally, this trial not only evaluates effectiveness, but also the costs associated with both interventions. Such a trial-based economic evaluation is important to determine whether DM cups, which are typically more expensive, are worthwhile in a population undergoing primary THP.

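### Randomisation is stratified by centre but the primary chi-square test is not; the test stays valid, and analysing by centre is a free, low-priority improvement

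*Protocol article*

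**What the plan says.** - **Randomization section.** "Variable randomization blocks of 2, 4, and 6 patients will be used, and we shall stratify for center". The Study design section gives the number of sites: "which will be conducted in 10 general and academic hospitals in the Netherlands".
- **Primary outcome analysis section.** The primary outcome "will be analyzed using chi-square analysis". Hospital appears in the next sentence: "Additional exploratory multivariable logistic regression analyses will adjust for clustering of data (e.g., at the hospital level".
- **Sample size calculation and Interim analysis sections.** Both also name the chi-square test; the interim allows Fisher's exact test if its assumptions fail.
- **Abstract.** "Data will be analyzed using multilevel models as appropriate for each outcome (linear/logistic/survival". The sentence does not mention the chi-square test. In the body, near-identical wording governs the secondary outcomes.
- **Discussion.** The authors intend to "compare groups in terms of dislocation rates with corresponding confidence intervals rather than strictly focusing on p-values".

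**The concern.** When randomisation is blocked within centres, the arms are balanced on centre by design. If centres differ in dislocation risk, that balance removes some chance variation from the treatment comparison. An unstratified test still counts that variation in its standard error, so it is slightly too cautious. Differences between centres are plausible here, because the Interventions section lets each hospital use its usual implants and its own care pathway.

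What is at stake is a little power and agreement between design and analysis. There is no risk of excess false positives. A secondary matter is that someone reading only the abstract would expect a multilevel model for the primary outcome.

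**Working it through.** **1. Reproduce the planned size.** Inputs from the Sample size calculation section: 4% against 1%, 80% power, α = 0.05. I take α as two-sided, as stated for the interim analysis. The mean rate is 0.025.

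- Without continuity correction: n = [1.96·√(2·0.025·0.975) + 0.8416·√(0.04·0.96 + 0.01·0.99)]² / 0.03² = (0.4327 + 0.1850)² / 0.0009 ≈ 424 per arm.
- With continuity correction: n′ = (424/4)·[1 + √(1 + 4/(424·0.03))]² ≈ 488.4 per arm.

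The stated 488 per arm is therefore the continuity-corrected figure. Exact power at 488 per arm is 88.3% for the uncorrected chi-square, 82.2% for the corrected one and 84.3% for Fisher's test.

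**2. Expected events.** 488·0.04 + 488·0.01 = 19.5 + 4.9 = 24.4 in total, or about 2.4 per centre over 10 centres.

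**3. Compare the two tests by simulation.** The stratified statistic is [Σ(aₖ − mₖn₁ₖ/Nₖ)]² / Σ[n₁ₖn₀ₖmₖ(Nₖ − mₖ) / (Nₖ²(Nₖ − 1))]. For centre k, aₖ is the events in one arm, mₖ the events in both arms, n₁ₖ and n₀ₖ the arm sizes, and Nₖ their sum. Arms are balanced 1:1 within centre. Centre effects are normal on the logit scale with an assumed SD. For each SD the intercept is re-solved so that the overall rates stay at 4% and 1% (power) or 2.5% in both arms (size). This matters: adding centre noise around logit(4%) and logit(1%) without re-solving lifts the overall rates to 5.9% and 1.6% at SD 1.0, which inflates power and no longer represents the protocol's assumption.

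Results for 488 per arm, 10 centres, 40,000 runs per setting; ranges cover equal and unequal centre sizes:

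| Centre SD | Size, chi-square | Size, stratified | Power, chi-square | Power, stratified |
|---|---|---|---|---|
| 0 | 4.94–5.12% | 4.94–5.12% | 88.4–88.7% | 88.4–88.7% |
| 0.3 | 4.94–5.03% | 4.95–5.04% | 87.9–88.1% | 88.0–88.1% |
| 0.6 | 4.74–4.83% | 4.82–4.89% | 86.3–86.9% | 86.4–87.0% |
| 1.0 | 4.49–4.78% | 4.76–5.04% | 83.1–84.8% | 83.6–85.3% |

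A separate run with 10 centres of 49 per arm gave power of 84.9% against 85.3% at SD 1.0 and 82.7% against 83.5% at SD 1.3. Size over that range was about 4.5–4.6% against 4.9–5.0%. A longer repeat of the size check (300,000 runs) gave 4.6% against 4.9% at SD 1.0 and 4.3% against 4.8% at SD 1.3. At SD 0.5 or below the tests differ by less than 0.1 points in both size and power.

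**4. The estimate that would accompany the test.** At the planned rates with 488 per arm, the unstratified risk difference is 3.0 points with standard error √[(0.04·0.96 + 0.01·0.99)/488] = 0.00995. The 95% interval is 3.0 ± 1.95, or 1.05 to 4.95 points.

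**The case against.** The strongest defence is that the chi-square test is valid, errs only towards caution, and matches the test used for the sample size and the interim analysis. Hospital clustering is also not ignored, since the exploratory regressions adjust for it. An SD of 1.0 is a large assumed effect: one SD multiplies a centre's odds of dislocation by about 2.7 (e^1.0). At more modest values nothing is gained. All of this stands, and it is why the point has low priority.

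Two stronger readings are tempting and are not supported.

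- **Two competing primary analyses.** A reader might infer from the abstract that the primary analysis can be chosen after the results are known. The abstract sentence speaks of data in general and does not single out the primary outcome. The Sample size, Interim analysis and Primary outcome analysis sections all name chi-square, and the regressions are expressly ranked as exploratory. What remains is a loosely worded abstract.
- **No effect estimate.** A reader might infer that the trial will report only a p-value. The Discussion commits to rates with confidence intervals, and a chi-square test does not preclude them. The effect scale and interval method are details that an article may leave to the full protocol or SAP.

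One caution applies to the remedy. With about 2.4 events expected per centre, centre-specific estimates would be unstable. Mantel–Haenszel methods pool across strata and tolerate this sparseness, so it affects the choice of estimator and is no reason to leave centre out.

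**Conclusion.** The point holds as a minor mismatch between design and analysis. The unstratified test is valid and at worst slightly conservative: it loses roughly 0.3 to 0.5 points of size and 0.4 to 0.8 points of power at an assumed between-centre SD of 1.0–1.3, and practically nothing at 0.5 or below. These figures rest on assumed normal centre effects on the logit scale, 10 centres, 1:1 balance within centre, and overall rates equal to the protocol's 4% and 1%. The trial's conclusions are not at risk, and no additional patients are needed.

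**What to change.** - Name the centre-stratified Cochran–Mantel–Haenszel test as the primary analysis, and state that no continuity correction is applied. That choice matters more than stratification itself: for the ordinary chi-square at 488 per arm it is the difference between 88.3% and 82.2% power.
- Report with it the dislocation rate in each arm and the Mantel–Haenszel risk difference with its 95% confidence interval, using a variance suited to sparse strata. This delivers the comparison that the Discussion favours.
- Keep the mixed logistic model as a sensitivity analysis.
- Reword the abstract's sentence so that multilevel models refer to the secondary and sensitivity analyses.

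The cost is a few sentences. The planned 488 per arm, or 550 with the allowance for loss, stays as it is, because it was derived with the more demanding continuity-corrected formula.
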